# Collaborative Assessment and Management of Suicidality (CAMS) compared to enhanced treatment as usual (E-TAU) for suicidal patients in an inpatient setting: study protocol for a randomized controlled trial

**DOI:** 10.1186/s12888-020-02589-x

**Published:** 2020-04-22

**Keywords:** Randomized controlled trial, Suicidality, Suicidal patients, Treatment, CAMS, Collaborative approach, Suicide prevention

## Abstract

**Background:**

The Collaborative Assessment and Management of Suicidality (CAMS) is a therapeutic framework that has been shown to reduce suicidal ideation and overall symptom distress. CAMS has not been previously evaluated in a standard acute inpatient mental health care setting with only short treatment times for suicidal patients. In this randomized controlled trial (RCT) we are investigating whether CAMS is more effective than Enhanced-Treatment as Usual (E-TAU) in reducing suicidal thoughts as primary outcome variable. We are also investigating depressive symptoms, general symptom relief, and the quality of the therapeutic alliance as secondary outcomes.

**Methods/Design:**

This RCT is designed as a single-center, two-armed, parallel group observer-blinded clinical effectiveness investigation. We are recruiting and randomizing 60 participants with different diagnoses, who are admitted as inpatients because of acute suicidal thoughts or behaviors into the Clinic for Psychiatry and Psychotherapy, Ev. Hospital Bethel in Bielefeld, Germany. The duration of treatment will vary depending on patients’ needs and clinical assessments ranging between 10 and 40 days. Patients are assessed four times, at admission, discharge, 1 month, and 5 months post-discharge. The primary outcome measure is the Beck Scale for Suicide Ideation. Other outcome measures are administered as assessment timepoints including severity of psychiatric symptoms, depression, reasons for living, and therapeutic relationship.

**Discussion:**

This effectiveness study is being conducted on an acute ward in a psychiatric clinic where patients have multiple problems and diagnoses. Treatment is somewhat limited, and therapists have a large caseloads. The results of this study can thus be generalizable to a typical inpatient psychiatric hospital settings.

**Trial registration:**

This clinical trial has been retrospectively registered with the German Clinical Trials Register; registration code/ DRKS-ID: DRKS00013727 (on January 12, 2018). In addition, the study was also registered with the International Clinical Trials Registry Platform of the World Health Organization (identical registration code). Registry Name: „Evaluation von CAMS versus TAU bei suizidalen Patienten – Ein stationärer RCT“.

## Background

Approximately 10,000 people die by suicide in Germany each year, with approximately 28 suicides per day or 1 suicide every 52 min [1]. More than 100,000 people attempt suicide every year in Germany. Over 90% of suicidal cases are associated with mental illness and/or acute crises and suicidality omnipresent within inpatient psychiatric settings [2, 3]. Nevertheless, there are surprisingly few empirically evaluated interventions and guidelines for the actual treatment of suicidal patients [4, 5], particularly within inpatient psychiatric settings.

Traditional treatment approaches for suicidal risk have typically targeted underlying mental disorders with limited proven effectiveness whereas a handful of suicide-focused clinical treatments have been shown to be effective for treating suicide risk through randomized controlled trials (RCT’s) [6]. There is extensive RCT support for Dialectical Behavioral Therapy (DBT) with borderline patients [7, 8], Brief Cognitive Behavioral Therapy (BCBT) for military personnel [9], Cognitive Therapy for Suicide Prevention (CT-SP) with suicide attempters [10] as well as Mindfulness-Based Cognitive Behavioral Therapy (MBCT) for chronically depressed outpatients [11]. Due to time, economic and personnel limitations, however, these treatments may be rarely used in routine clinical practice and may only be effective after a certain prohibitively long duration of therapy. In the case of acute risk of suicidal risk, however, immediately effective shorter-term interventions are needed. Leading suicidologists repeatedly have asked, whether treatment focusing on the mental disorder only is an effective way to reduce the risk of suicide [12–14]. Some have proposed that it might be necessary to focus treatment on suicidal risk as an independent syndrome early in care irrespective of the underlying disorder. Indeed, the establishment of research criteria for suicidal behaviour disorders within the DSM-5 reflects a growing appreciation of this idea. Within their systematic review and meta-analysis, Meerwijk et al. note that psychotherapeutic interventions that directly target suicidal thoughts and behaviours are more effective in reducing suicide attempts and suicidal ideation than interventions that only address these factors indirectly [15]. Consequently, within the contemporary suicide treatment research, there is an increasing emphasis to develop effective treatment approaches that quickly and directly engage the issue of suicidal risk independent of psychiatric diagnoses.

Along these lines, the Collaborative Assessment and Management of Suicidality (CAMS) is a treatment framework for suicidal patients that specifically focuses on patient-defined difficulties and challenges that make consider suicide (referred to as “drivers” within the approach) [13]. CAMS is thus a semi-structured therapeutic framework in which the therapist and the patient engage in as assessment and intervention process that is expressly designed to reduce suicidal risk. CAMS emphasizes an active collaboration between the patient and the therapist which is meant to enhance the therapeutic alliance while increasing the patient’s motivation to live. To date, CAMS is supported by a range of clinical trial studies including eight correlational nonrandomized published trials [13] and four published RCT’s [16–19]. So far, results are promising and suggest that CAMS is superior to other approaches and leads to a rapid and sustained reduction of suicidal ideation, overall symptom distress, and related secondary risk factors such as depression and hopelessness. The impact of CAMS on self-harm and suicide attempts is promising but limited thus far [16]. The usefulness of CAMS in longer and private inpatient settings has already been previously demonstrated [20, 21]. Ryberg et al. have shown CAMS to be effective with combined samples of suicidal inpatients and outpatients [19]. But to further confirm and generalize such results to a broader population requires further research. Thus, there is a need for additional randomized controlled trials with comparable treatment doses of CAMS and TAU within an inpatient context of a standard psychiatric sample of a public health system with a short duration of treatment. Moreover, no CAMS clinical trial studies to date have been carried out in German-speaking countries.

## Method

### Aim of the trial

The primary aim of the current study is to investigate whether CAMS reduces suicidal ideation and suicidal behaviours more than Enhanced Treatment As Usual (E-TAU) within a sample of suicidal inpatients. Secondary aims are to investigate the effects of CAMS versus E-TAU on general symptom burden, depression, reasons for living, and the therapeutic relationship. Furthermore, we plan to test the influence of various moderating variables on treatment outcomes; possible moderators will include diagnostic group (borderline personality disorder in particular), number of previous suicide attempts, treatment duration, number of therapeutic sessions, and baseline levels of psychiatric distress (see [22] for more information on previous moderators of CAMS).

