### Trial design

In our pragmatic randomized controlled trial at the Clinic of Psychiatry and Psychotherapy, Ev. Hospital Bethel, Germany, CAMS is being compared to E-TAU within an inpatient crisis setting. The trial is designed as a single-center, two-armed, parallel-group, observer-blinded randomized clinical effectiveness trial. Since we assume that about 50% of the patients we initially examine do not meet the inclusion criteria, 20% do not consent to participate in the study and 20% discontinue treatment, we plan to examine 144 patients of the Clinic who are admitted to the ward due to acute suicidal risk (thoughts or behaviors) in order to obtain our target sample size of 60 patients. After screening and randomizing, the study participants will be followed for about 6 months at four checkpoints t_1_, t_2_, t_3,_ t_4_.

Individuals who are screened positive for the trial and who gave their written informed consent to take part in the study are asked to complete a set of questionnaires (t_1_) on the admission day or on the workday following the admission day. Then, the patient is randomized and informed about their group membership and the respective interventions begin on the following day. A second follow up assessment (t_2_) is carried out between 10 and 40 days later at the day before discharge. Another follow-up assessment will be arranged for 4 weeks after discharge (t_3_). Five months after the end of treatment, patients will receive the assessment instruments again by mail (t_4_). Refer to Fig. 1 for a schematic overview of the time flow of the trial and see Appendix 1 for the complete review of the study questionnaires.

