There are no mandatory homework assignments during a CAMS course of care. The duration of CAMS-guided care is dependent on the treatment progress and varies between patients. The treatment is concluded when the clinician and the patient agree that the acute danger of a suicidal act is eliminated, adaptive coping skills are developed while the patient scores him/herself below 3 on subjective suicidal risk rating (on a 5-point scale) and that they are managing any suicidal thoughts or feelings while remaining behaviorally stable which may trigger discharge from the inpatient setting. In the present RCT, cases who have received between 4 and 9 CAMS sessions including the initial session will be analysed. See Appendix 2 for the complete CAMS Material.

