### Data analyses

#### Statistical analyses

The analysis of this study will be calculated as a mixed-effects model with the BSS total symptom score as the outcome variable. Mixed models are especially suited for longitudinal studies as they can deal with a correlated data structure and can analyze all cases and data points, even if missing values occur in the course of the trial. In detail, participants will be modeled as a random factor, while time and intervention (CAMS vs. TAU) as well their interaction will be modeled as fixed factors. The hypothesis that CAMS is superior to TAU in the treatment of suicidal patients will be evaluated by the significance test of the interaction effect time × intervention.

In case of a significant interaction effect, two planned general linear hypotheses will be calculated as post-hoc tests for linear mixed effect models in order to test between-group differences at t_2_ and t_3_. *P*-values will be adjusted for multiple comparisons following the Holm procedure.

We will perform an intention-to-treat analyses, that is, all trial participants will be analyzed as randomized, even if they discontinue treatment or are unavailable for one or both of the follow-up interviews. The between-group effect size (Cohen’s d) will be calculated at each follow-up assessment (t_2_ and t_3_).

Continuous secondary outcome measures (BDI-II, SCL-18-Mini, B-RFL, D-STAR-P) are analyzed in the same way. In absence of a valid cut-off score for clinically significant change or treatment response of the BSS, the number of subjects with clinically significant improvement as well as worsening based on the reliable change index (RCI) will be compared between groups using χ2 –tests or Fisher’s exact tests. For this purpose, the RCI will be calculated based on the pre-treatment scores of the study sample. We will use two-tailed tests for statistical significance with alpha set at *P* < 0.05. Effect strength will be determined with Cohen’s d. All calculations will be performed using SPSS 20.0 computer software [48].

We also investigate whether there is a correlation between the number of sessions and the effect of the therapeutic treatment using a correlation analysis.

Interim analyses before the completion of the investigations are not intended. Any potential deviations from the original statistical plan as defined in the study protocol will be described in protocol amendments as well as in the final study report.

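### Treatment duration and number of sessions arise after randomisation and depend on clinical course, so they are not valid moderators and their correlation with outcome cannot be read as a dose effect

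*Protocol article*

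**What the plan says.** Under Aim of the trial, the protocol article puts two kinds of variable in one list: "possible moderators will include diagnostic group (borderline personality disorder in particular), number of previous suicide attempts, treatment duration, number of therapeutic sessions". Baseline distress closes the list in the same sentence.

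Under Statistical analyses it adds: "We also investigate whether there is a correlation between the number of sessions and the effect of the therapeutic treatment using a correlation analysis".

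On timing, Trial design states: "Then, the patient is randomized and informed about their group membership and the respective interventions begin on the following day". The t2 assessment is set for the day before discharge.

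On what determines length, the abstract says for the whole trial: "The duration of treatment will vary depending on patients’ needs and clinical assessments ranging between 10 and 40 days". For the experimental arm, the CAMS section is explicit: "The duration of CAMS-guided care is dependent on the treatment progress and varies between patients". It continues: "The treatment is concluded when the clinician and the patient agree that the acute danger of a suicidal act is eliminated", together with conditions on coping skills, the patient's own risk rating and behavioural stability. The E-TAU section gives no ending rule tied to progress. It says that session numbers match CAMS, at about two per week and up to nine.

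**The concern.** A moderator analysis asks whether the effect of assignment differs between kinds of patient, so the moderator must be fixed before assignment. Diagnostic group, previous attempts and baseline distress meet that condition (the confirmatory SCID interview follows baseline, but the diagnosis it records is a pre-existing characteristic). Duration and session count do not. They are produced during treatment and partly by the course of the suicidality that the trial measures.

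The correlation has the same weakness. A patient may have few sessions because of quick recovery, and many because of severe illness at entry. The t2 assessment also moves with discharge, so long stayers have had more time to change. Severity, speed of response, elapsed time and dose cannot be separated by correlating sessions with change. A patient's own change from baseline is also not that patient's treatment effect.

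At stake is a secondary conclusion about how much CAMS is needed, or for whom, that the data could not support.

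**Working it through.** The plan gives no figure for these analyses, so there is none to reproduce. The check has two parts: when the variables arise, and what the planned analyses return when sessions have no effect at all.

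**1. Timing and determinants**

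| Variable | Fixed before randomisation? | Determined by |
|---|---|---|
| Diagnostic group | Yes | patient history |
| Previous suicide attempts | Yes | patient history |
| Baseline distress | Yes | t1 assessment |
| Treatment duration | No | needs and clinical assessments; in CAMS, progress |
| Number of sessions | No | duration, at about two per week |

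**2. Model A: improvement directly shortens the stay**

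From the protocol: 30 patients per arm and 4 to 9 sessions. Assumed: improvement I has SD 1 and the arms do not differ (d = 0). A latent length is L = -ρ·I + √(1-ρ²)·ε, and sessions = round(6.5 + 1.5·L), limited to 4 to 9. The dependence ρ is an assumption, because the documents give none. There were 4,000 simulated trials per row, with two-sided tests at 5%.

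| ρ in CAMS / E-TAU | Mean r (sessions, improvement) | r significant | Arm × sessions significant |
|---|---|---|---|
| 0 / 0 | 0.00 | 5% | 5% |
| 0.3 / 0.3 | -0.29 | 63% | 5% |
| 0.5 / 0.5 | -0.48 | 98% | 5% |
| 0.3 / 0 | -0.14 | 20% | 19% |
| 0.5 / 0 | -0.24 | 47% | 48% |

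The correlation is misleading in every row with ρ above zero in at least one arm. The interaction test departs from 5% only when the link differs by arm.

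With a true arm effect of d = 1 and equal ρ, adding sessions and their interaction lowered the estimated arm effect from 1.00 to 0.91 (ρ = 0.3) or 0.76 (ρ = 0.5). The arm term of such a moderator model would therefore also be biased.

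**3. Model B: discharge at a threshold**

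Assumed: daily severity is a mean falling by 0.02 to 0.05 SD per day, plus a person effect, plus autocorrelated noise (0.95). Discharge falls on the first day from day 10 on which a noisy self-rating is below a threshold, and at the latest on day 40. Sessions = round(days × 2/7) + 1. There were 200,000 patients per scenario, and sessions again had no effect.

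- Sessions with baseline severity: r = 0.55 to 0.66.
- Sessions with t2 severity: r = 0.52 to 0.67.
- Sessions with t1-to-t2 improvement: r = +0.11 to +0.21.

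Power to detect the last of these at N = 60, by Fisher z:

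- r = 0.11: atanh(0.11)·√57 = 0.110 × 7.55 = 0.83, which gives about 13%.
- r = 0.21: 0.213 × 7.55 = 1.61, which gives about 36%.

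One limit of Model B is that its session formula exceeds the protocol's maximum of nine. Day 30 gives 30 × 2/7 = 8.6, rounded to 9, plus 1 = 10. Day 40 gives 11.4, rounded to 11, plus 1 = 12. Its magnitudes are illustrative only.

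**4. Comparison**

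The true dose effect is zero in both models, yet the correlation with improvement is negative in A and positive in B. In A, fast improvers leave early. In B, patients who are more severe at entry stay longer and have more time and more room to improve.

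**The case against.** The wording is modest. The protocol speaks of possible moderators and of investigating a correlation, and it nowhere claims a causal dose effect. Model form and labelling may sit in an analysis plan that is not shown, and describing how sessions relate to outcome is legitimate. That stands, and it is why the analyses need relabelling rather than deletion. It does not rescue the moderator list, which the article itself fixes and which puts two post-randomisation variables beside baseline ones without distinction.

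A reader might go further and infer any of the following. The documents do not support them.

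- *The results will be spurious, showing that more sessions go with worse outcomes.* Direction and size depend on how progress drives length, which the documents do not quantify. The two models give opposite signs for improvement.
- *The moderator test must give false positives.* With an equal link in both arms it kept about 5% error. The explicit progress rule is written for CAMS only, which makes an asymmetry possible. However, the abstract ties duration to needs and assessments in all patients, and session numbers are meant to be comparable, so a link in CAMS alone is not established.
- *Session count is simply length of stay.* At two per week they run together, but the limit of nine breaks the tie in stays beyond about four weeks.
- *The CAMS ending rule is a single self-rating threshold.* It combines several conditions, so Model B simplifies it.

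**Conclusion.** The point holds as one of interpretation. Duration and session count follow randomisation and depend on needs, clinical assessment and, in CAMS, progress. They are not valid effect modifiers, and the sessions correlation is confounded by severity and speed of response.

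The size cannot be derived from the documents. With no true dose effect, the assumptions tried gave correlations with improvement from about -0.5 to +0.2. That range is illustrative and not a bound. The interaction test is at risk mainly if the link between progress and length differs by arm, with 19% to 48% false positives under the assumed CAMS-only link of 0.3 to 0.5.

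The primary test, time by intervention in the mixed model, uses neither variable and is unaffected. The matter concerns secondary analyses only.

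**What to change.** In Aim of the trial, limit the moderator list to variables fixed before randomisation: diagnostic group including borderline personality disorder, number of previous suicide attempts, and baseline distress. Label these analyses exploratory.

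In Statistical analyses, present number of sessions and length of stay by arm as descriptive process data. Any association of sessions with outcome may be reported there too, with a statement that both variables follow randomisation and may reflect severity and response, and with no moderator or dose-response claim.

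This is a change of wording and needs no new data. The downside is that one planned secondary inference, on the relation of dose to effect, is given up.

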### Trial design

In our pragmatic randomized controlled trial at the Clinic of Psychiatry and Psychotherapy, Ev. Hospital Bethel, Germany, CAMS is being compared to E-TAU within an inpatient crisis setting. The trial is designed as a single-center, two-armed, parallel-group, observer-blinded randomized clinical effectiveness trial. Since we assume that about 50% of the patients we initially examine do not meet the inclusion criteria, 20% do not consent to participate in the study and 20% discontinue treatment, we plan to examine 144 patients of the Clinic who are admitted to the ward due to acute suicidal risk (thoughts or behaviors) in order to obtain our target sample size of 60 patients. After screening and randomizing, the study participants will be followed for about 6 months at four checkpoints t_1_, t_2_, t_3,_ t_4_.

Individuals who are screened positive for the trial and who gave their written informed consent to take part in the study are asked to complete a set of questionnaires (t_1_) on the admission day or on the workday following the admission day. Then, the patient is randomized and informed about their group membership and the respective interventions begin on the following day. A second follow up assessment (t_2_) is carried out between 10 and 40 days later at the day before discharge. Another follow-up assessment will be arranged for 4 weeks after discharge (t_3_). Five months after the end of treatment, patients will receive the assessment instruments again by mail (t_4_). Refer to Fig. 1 for a schematic overview of the time flow of the trial and see Appendix 1 for the complete review of the study questionnaires.

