### Measures taken to minimize/avoid bias, including randomization and blinding

#### Randomization

Patients who meet the inclusion criteria and agree to participate in the study are randomly assigned to one of the two therapy arms either CAMS (36 subjects) or TAU (36 subjects). Randomization is performed by an independent practitioner by throwing the dice immediately after the patients have agreed to participate in the study and returned the completed questionnaires (1–3 = CAMS, 4–6 = E-TAU).

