### Statistics

#### Power analysis and sample size calculation

An a priori power analysis by using G*Power was carried out to determine the sample size [47]. On the basis of the available literature, we expect an average effect size (comparison of CAMS versus TAU with regard to the reduction of suicidal tendencies) of Cohen’s d = 1. Here we refer to the study by Ellis (2015), which is rather comparable [21]. The author reports a pre-post effect size of d = 1.72 for CAMS (measured by the BSS) and of d = 0.71 for TAU. Although the interaction effect was not reported we assume it to be about d = 1.

Taking into account a probability of α error = 5% (one-sided) and a power of 1 - β = 80%, the total sample size of 48 participants, i.e. 24 per group. For compensating participants who withdraw their consent we plan 30 subjects per group. Assuming that after the first diagnostic examination 50% are not eligible for inclusion into the study due to non-existent inclusion criteria or exclusion criteria and 20% discontinue treatment in the course of the study or are excluded due to further inpatient treatment, it is to be expected, that 144 patients have to be interviewed, of whose 72 patients (36 per group) are randomly assigned to CAMS intervention (36 subjects) and a TAU (36 subjects), respectively, in order to achieve the targeted number of *N* = 2 × 30 in the intent to treat sample.

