**Table Taba:** 

Version	Author	Date	Reason for Revision
0.1	[name]	1 March 2019	1st draft version sent to participating authors for review
0.2	[name]	24 May 2019	2nd draft version with integrated feedback from all co-authors sent to all co-authors again
1.1	[name]	29 May 2019	1st version sent for review
1.2	[name]	March 2020	2 ^nd^ revised version

Date: 29 May 2019

The trial opened by recruiting the first patient on 8 March 2017 and is still recruiting. Recruitment is terminated when the targeted number of 30 patients in each treatment group has been reached. Recruitment is expected to be completed in autumn 2019.

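### The recruitment figures do not follow from the stated rates, and the number to be randomised is given as both 60 and 72

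*Protocol article*

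**What the plan says.** The figures appear in five places in the protocol article.

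- **Abstract, Methods/Design:** "We are recruiting and randomizing 60 participants with different diagnoses".
- **Trial design:** "Since we assume that about 50% of the patients we initially examine do not meet the inclusion criteria", and further that "20% do not consent to participate in the study and 20% discontinue treatment, we plan to examine 144 patients of the Clinic". The stated purpose is "in order to obtain our target sample size of 60 patients".
- **Randomization:** patients are "randomly assigned to one of the two therapy arms either CAMS (36 subjects) or TAU (36 subjects"). On the method: "Randomization is performed by an independent practitioner by throwing the dice", with three faces of the die for each arm. No blocking or other restriction is described.
- **Power analysis and sample size calculation:** the calculation gives 48 participants, raised to 30 per group to allow for withdrawn consent. With 50% not eligible and 20% discontinuing or excluded because of further inpatient treatment, "144 patients have to be interviewed, of whose 72 patients (36 per group) are randomly assigned". The 2 × 30 that results is described as the intention-to-treat sample.
- **Trial status:** "Recruitment is terminated when the targeted number of 30 patients in each treatment group has been reached".

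The Statistical analyses section defines intention to treat as analysing all participants as randomised, including those who stop treatment or miss follow-up interviews.

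**The concern.** A reader needs three things from these sections: how many patients will be randomised, how many must be examined to get there, and what event ends recruitment. The article answers each of them, but the answers disagree. The examined-to-target figure does not follow from its own rates, and the randomised total differs between sections. The stopping rule uses a count whose meaning is not given.

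What is at stake is whether the trial can be judged against its plan. If the report shows 60, 66 or 72 randomised, nobody can say from this document whether the trial finished as planned, stopped short or over-recruited. It also matters whether patients who leave are replaced. Recruiting until 30 per arm are retained is a different design from randomising a fixed number and analysing all of them.

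**Working it through.** **Inputs.** Trial design: 144 examined, 50% ineligible, 20% refusing, 20% discontinuing, target 60. Sample size section: 144 examined, 50% ineligible, 20% lost, 72 randomised, target 60, with no refusal rate. Randomization: 36 + 36, one die throw per patient at 1:1.

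**Step 1. Reproduce the plan's figures.** They come back only as 60 × 1.2 = 72 randomised and 72 / 0.5 = 144 examined. This adds 20% to the target instead of dividing by the retained share, and applies no refusals.

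**Step 2. Trial design rates applied in sequence.**

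| Stage | Calculation | Patients |
|---|---|---|
| Examined | – | 144 |
| Eligible | 144 × 0.5 | 72 |
| Consenting, so randomised | 72 × 0.8 | 57.6 |
| Completing treatment | 57.6 × 0.8 | 46.1 |

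Other readings do not give 60 either. Adding the two 20% rates gives 72 × 0.6 = 43.2. Taking all three rates on the 144 gives 144 × 0.1 = 14.4.

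**Step 3. Sample size section rates.** 144 × 0.5 = 72 randomised, then 72 × 0.8 = 57.6 completing, which is 2.4 short of 60. Going from 72 to 60 is a loss of 12/72 = 16.7%, not 20%.

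**Step 4. The correct inversions.**

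- 60 completers at 20% loss: 60 / 0.8 = 75 randomised.
- 75 randomised under the Trial design rates: 75 / (0.5 × 0.8) = 187.5, so 188 examined.
- 60 randomised under the Trial design rates: 60 / (0.5 × 0.8) = 150 examined, with 60 × 0.8 = 48 expected to complete treatment.

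**Step 5. The randomised totals side by side.** Abstract: 60. Randomization and sample size sections: 72. The sample size section calls 60 of those 72 the intention-to-treat sample. Under the Statistical analyses section that sample is everyone randomised, so with 72 randomised it is 72, and it is 60 only if 60 are randomised.

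**Step 6. The stopping rule under dice allocation.** Let N be the number randomised when both arms first reach 30. For n of at least 60, P(N ≤ n) is the probability that a Binomial(n, 0.5) count lies between 30 and n − 30. This gives:

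- mean N about 66, median 65, 5th to 95th percentile 60 to 77;
- P(N = 60) = 10.3%;
- P(N > 72) = 12.5%.

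Recruitment stops when the smaller arm reaches 30, so every patient beyond 60 is in the other arm. These figures take 30 to mean randomised patients. If it means retained patients, the total is larger.

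**The case against.** The best defence reads 60 as the completers out of 72 randomised. That would remove most of the conflict between 60 and 72 and leave only a small error (57.6 against 60, or 72 against 75). The text does not allow it. The abstract says 60 are randomised, and the sample size section labels the 60 as intention to treat, which the analysis section defines as all randomised patients. It would also leave the refusal rate in the Trial design section unused.

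Other parts of the defence do stand.

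- **144 is a forecast.** Recruitment ends on patients per group, not on the number examined. If the yield is lower, more patients are examined, and the ward has about 600 admissions a year.
- **60 and 30 per group are nominally the same number.** The conflict in totals is 60 against 72. The stopping rule adds the separate problem that 30 is undefined.
- **Dice are not in themselves an error.** 36:36 can be read as the expected split, and a surplus in one arm does not reduce power.

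A reader might infer that 46 patients falls below the 48 of the power calculation, so that the trial is underpowered. The documents do not support this. The second 20% concerns leaving treatment, and the plan analyses all participants as randomised, including those who discontinue. Also, 48 is more than the stated inputs require: d = 1, one-sided 5% and 80% power need about 14 per group in a t-test. At 23 per group the power at d = 1 is about 95% one-sided and 91% two-sided.

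A reader might also infer that one 20% allowance is counted twice, from 48 to 60 and again from 60 to 72. The article gives the two steps different reasons, withdrawn consent for the first and discontinuation or further inpatient treatment for the second, so this is not shown to be a mistake.

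**Conclusion.** The point holds as an error of arithmetic and consistency in the stated trial size. Under the Trial design rates, 144 examined gives 57.6 randomised and 46.1 completing treatment, and no reading tried gives 60. Under the sample size section's rates it gives 57.6 completing. The randomised total is stated as 60 in one place and 72 in two others, and the intention-to-treat label fits 60 only if 60 are randomised. The rule that ends recruitment does not say whether 30 counts randomised or retained patients. On the first reading it gives a random total averaging about 66.

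This rests on applying the rates one after another, as screening, consent and treatment follow one another, and on independent fair throws with no restriction on the allocation. It does not establish a power shortfall at d = 1; whether d = 1 is credible is a separate question. Nor does it show that the allocation method must change. Blocks stratified by therapist would balance the arms, but the same two unblinded therapists treat both arms and might foresee assignments, and the article expected recruitment to end in autumn 2019.

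**What to change.** Use one set of numbers in the abstract, Trial design, Randomization, the sample size section and Trial status. Two consistent choices are:

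- **60 randomised as the intention-to-treat sample:** about 150 examined under the Trial design rates, with about 48 expected to complete treatment. This agrees with the abstract.
- **60 completers:** 75 randomised and about 188 examined, with the intention-to-treat sample stated as 75.

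Apply the refusal rate in both the Trial design and sample size sections, or in neither, and keep the intention-to-treat label for everyone randomised. State that 30 per group counts randomised patients and that those who discontinue are not replaced. With the second choice, the per-group figure for randomised patients has to be restated to match 75. End recruitment on the total randomised, not when the smaller arm reaches 30, and describe equal group sizes as expected under dice allocation.

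The cost is a text correction in five places. The first choice adds no patients to the abstract's figure; the second adds 15 randomised. If recruitment has already closed, report the totals actually examined and randomised, and say which rule ended recruitment.
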